#### Secondary outcomes

The following variables will also be assessed:Body fat and body mass percentages, determined by TANITA, a bioimpedance scale.*Quality of life-QLI* [37, 38]: This includes 10 items, with a multiple-choice Likert response format on a scale from 1 to 10. It evaluates ten areas: physical, psychological, self-care and independent functioning welfare, occupational functioning, interpersonal functioning, social-emotional support, community and support services, personal fulfillment, spiritual fulfillment, overall perception of quality of life.*International Physical Activity Questionnaire - IPAQ - short* [39]: Self-report containing seven items that collect information about physical activity (PA) and sedentary behaviour in four areas: activity at work, when traveling, at home and during leisure time (leisure). The IPAQ addresses the number of days and minutes spent performing physical activities such as leisure-time occupations, locomotion and housework activities. The score is derived from the number of days, hours and minutes employed in these activities [40].

To assess treatment moderators, the following variables will also be measured:*GSES-12 Self-Efficacy Questionnaire General* [41, 42]: A self-report scale consisting of 10 items with a 4-point Likert scale. It was designed to assess overall efficacy and it evaluates the stable sense of personal competence to effectively manage a variety of stressful situations.*BREQ-2 - Behavioural Regulation in physical exercise and eating habits questionnaire* [43, 44]: The original questionnaire was developed to measure external regulation, introjected, identified and intrinsic motivation. The BREQ-2 scale consists of 19 items, compared to 15 on the original scale, which measure stages of the self-determination continuum on a 5-point Likert scale ranging from 0 (not true for me) to 4 (completely true for me), and adds the motivation factor. An adaptation of this scale can also be used to assess motivation to change eating habits.*Expectations about treatment* -adapted from Borkovec & Nau [45]: 6-item scale that uses a 10-point Likert scale. It evaluates user expectations about the online programme they will receive.*Satisfaction with treatment -* adapted from Borkovec & Nau [45]: 6-item scale with a 10-point Likert scale. It evaluates the user’s opinion about the programme received in terms of satisfaction and usefulness.

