### Instruments

Participants in the SII condition will have four assessments: pre-intervention, post-intervention (3 months), Follow-up 1 (6 months), and Follow-up 2 (12 months). Measurements regarding satisfaction with the treatment will be filled out after each intervention module. Participants in the UCM condition will have two assessments: pre-intervention, post-intervention (3 months). At that time they will be invited to receive the Internet-based intervention. All the UCM participants who accept will be assessed again at 6 months (post-intervention), and Follow-up 1 (9 months) and Follow-up 2 (15 months). All the UCM participants who decided not to participant will be assessed at Follow-up 1 (6 months), and Follow-up 2 (12 months). The variables and assessment times are summarised in Table 1.

**Table 1 Tab1:** Study variables and assessment points

Assessment area	Instrument	Time of assessment
Primary outcomes		
Blood pressure	Omron®	Baseline, post-T and follow-ups
BMI	TANITA	Baseline, post-T and follow-ups
Secondary outcome		
Gender, age	Sociodemographic question.	Baseline
Body fat and mass	TANITA	Baseline, post-T and follow-ups
Quality of life	QLI	Baseline, post-T and follow-ups
Other measures		
Physical activity	IPAQ	Baseline, post-T and follow-ups
Self-efficacy	GSES	Baseline, post-T and follow-ups
Intrinsic motivation	BREQ-2	Baseline, post-T and follow-ups
Treatment expectations	Treatment expectations	Baseline
Treatment satisfaction	Treatment satisfaction	Post-T

Follow-up sessions: Post-treatment, 6 and 12 months follow-ups

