## Discussion

Overweight and obesity are considered chronic conditions and their relationship as a promoter and potentially aggravating factor of hypertension is clearly recognised [46]. Hypertensive patients generally have unhealthy and sedentary habits. Universal non-targeted lifestyle interventions for weight loss are not sufficient for this population because they have specific demands and health conditions, in addition to health risks and medical treatments, that differ from other obese populations [26].

Studies assessing the efficacy of online interventions to change lifestyles in this hypertensive population are still scarce. From a public health perspective, it is necessary to develop programmes that promote healthy lifestyles in these patients and prevent the early stages of obesity before new diseases appear and increase the likelihood of cardiac complication associated with excess body weight [26, 47].

This study will be applied in the hypertension unit of a public hospital. Among the benefits of using the programme “Vivir Mejor” (Living Better), we would like to highlight: (a) it is a completely self-guided programme; (b) with the advantage of empowering patients, increasing their perception of self-efficacy, and making the patient the promoter and the person responsible for changing their lifestyles; (c) a low associated cost, as it does not need the supervision of clinical staff; (d) the potential to reach many people, with no time or geographical restrictions; (e) the possibility of continuously monitoring a patient’s progress during treatment without physical visits and (f) it introduces innovative technologies and treatments to aid health professionals in their daily work in public health contexts. Thus, with only a computer, patients will have access to an intervention to produce changes in lifestyle, with a focus on the two pillars indicated by the WHO: diet and physical activity.

The possible limitations of this study are: (a) a bias in the samples, as participants with no Internet access are excluded, and (b) it is not a multicentre study, as the patients will be selected just from one health centre.

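### Satisfaction with treatment is listed as a treatment moderator, but it is measured only after treatment starts and rates a programme the usual-care arm has not received at the 3-month comparison

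*Protocol article*

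**What the plan says.** Under Secondary outcomes, the protocol article introduces a second group of scales with "To assess treatment moderators, the following variables will also be measured". Four follow: general self-efficacy, BREQ-2 motivation, treatment expectations, and satisfaction with treatment. The last is defined as the user's "opinion about the programme received in terms of satisfaction and usefulness".

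The Instruments section, in its description of the SII schedule, states: "Measurements regarding satisfaction with the treatment will be filled out after each intervention module". Table 1 in that section gives post-treatment as the only time for this scale and files it under other measures. Self-efficacy and BREQ-2 are scheduled at baseline, post-treatment and follow-ups, and expectations at baseline only.

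UMC participants are assessed before the intervention period and at 3 months. Of the 3-month visit the section says: "At that time they will be invited to receive the Internet-based intervention".

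The Statistical data analysis section plans 2×2 mixed ANOVAs (condition by pre/post) and mentions multilevel regression. It gives no model for moderators.

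**The concern.** A moderator is a characteristic that treatment cannot have altered and that is defined in both arms, so that the randomised treatment effect can be compared across its levels. Satisfaction with the programme fails on both counts: it arises from exposure to the programme, and up to 3 months it exists in one arm only.

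If the assigned role were carried into analysis, the likely report would be that the programme works better in satisfied patients. Such a pattern can appear when the effect is the same for everyone, because patients who are doing well, or who would have done well anyway, may rate the programme more highly. It would be a poor guide to whom the programme should be offered, since satisfaction is unknown when that decision is made.

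**Working it through.** The plan gives no figure for moderation, so there is none to reproduce. The check has three steps.

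**1. Timing and arm, from Secondary outcomes, Instruments and Table 1**

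| Listed variable | Baseline value | Defined in UMC up to 3 months |
|---|---|---|
| Self-efficacy | yes | yes |
| BREQ-2 | yes | yes |
| Expectations | yes | yes, if completed before allocation is disclosed |
| Satisfaction | no | no |

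The text (after each module) and Table 1 (post-treatment) differ on when satisfaction is collected. Both times fall after randomisation and exposure, so the conclusion is the same under either.

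**2. Can the interaction be estimated?** Let A = 1 for SII and 0 for UMC, and let S be satisfaction. A moderator regression uses the columns 1, A, S and A×S.

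- If S is left missing in UMC, every control drops out and no between-arm contrast remains.
- If S is set to a constant such as 0 in UMC, then A×S equals S in every row. The matrix has rank 3 with 4 columns, and the coefficients of S and A×S cannot be separated.

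**3. What would the feasible substitute show?** The analysis that could still be run is to split SII at the median of satisfaction and compare each half with all controls. Assumptions:

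- the true effect is 0.64 SD for every patient (the effect size in the Sample size section), so there is no moderation;
- within SII, satisfaction and outcome are bivariate normal with correlation r, the outcome has SD 1, and higher is better;
- r is not given in the article, so a range is shown.

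A median split shifts the mean outcome of each half by r × √(2/π) = 0.798 × r, upwards in the satisfied half and downwards in the other.

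| r | Shift | Apparent effect, high satisfaction | Apparent effect, low satisfaction | Gap |
|---|---|---|---|---|
| 0 | 0 | 0.64 | 0.64 | 0 |
| 0.3 | 0.798 × 0.3 = 0.24 | 0.64 + 0.24 = 0.88 | 0.64 − 0.24 = 0.40 | 0.48 |
| 0.5 | 0.798 × 0.5 = 0.40 | 0.64 + 0.40 = 1.04 | 0.64 − 0.40 = 0.24 | 0.80 |

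A simulation with 400,000 draws per arm gave the same values to two decimals at r = 0.3 and 0.5, and 0.64 in both halves at r = 0. The whole gap comes from selecting on a post-randomisation variable.

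**The case against.** The best defence is that the article never describes the analysis criticised here. The Statistical data analysis section contains no interaction with satisfaction and no satisfaction subgroup, and moderator models are commonly left to a statistical analysis plan. Table 1 gives satisfaction a neutral label, and its collection in SII already suits a descriptive report. The correlations and the median split above are illustrations, not the plan's.

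All of that stands, and it limits the size of the point. It does not remove it. The Secondary outcomes section assigns the moderator role in so many words, nothing elsewhere withdraws it, and no later model could make it valid for the randomised comparison.

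A reader might infer more than the document supports in three places:

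- **Self-efficacy and BREQ-2.** These are measured repeatedly, and the Discussion names "increasing their perception of self-efficacy" among the programme's benefits. One might conclude that values affected by treatment will be used as moderators. No passage says so. Both scales have baseline values, and a variable that treatment may later change can still be a sound moderator at baseline.
- **Reverse causation as the only reading.** Ratings after early modules precede the 3-month blood pressure and BMI measurements, so an association within SII need not mean that good results caused satisfaction. Those ratings are still post-randomisation, and the UMC patients who would have given the same ratings cannot be identified.
- **Controls never rating the programme.** UMC patients who accept it at 3 months are assessed again afterwards and could rate it. They do so after the randomised comparison has ended, and they are a self-selected group.

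**Conclusion.** The point holds for satisfaction alone, one of the four variables listed for moderation. At the 3-month randomised comparison its interaction with condition cannot be estimated, and a split of SII by satisfaction can show moderation where none exists. The first conclusion follows from the schedule and needs no assumption. The size of the second depends on an unknown correlation: the spurious gap is 0 at r = 0, 0.48 SD at 0.3 and 0.80 SD at 0.5, under normality, a median split and a uniform effect of 0.64 SD.

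This is a minor correction to a secondary analysis. The primary outcomes, the listed ANOVAs and the sample size do not depend on it.

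**What to change.** - Remove satisfaction from the variables introduced as moderators. Describe it as an acceptability or process measure, reported descriptively among programme recipients, with UMC patients who later take up the programme shown separately.
- State that moderator analyses are exploratory condition × baseline interactions, using the baseline values of self-efficacy, BREQ-2 and expectations. The Procedure section places the first assessment before patients learn their allocation, so all three can serve if both arms complete them at that visit.
- While editing, make the text and Table 1 agree on when satisfaction is collected.

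The cost is a few sentences. No new data, patients or visits are needed.

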### Statistical data analysis

SPSS v.20 will be used for statistical analysis. Relevant statistical analyses will first be performed to verify proper randomization (independent samples *t* test for equivalence of groups). Intention-to-treat and per-protocol analysis will be used. Descriptive statistics for the variables included (mean and 95% confidence interval for normally distributed quantitative variables; and median and interquartile range for abnormally distributed quantitative variables) will be performed. A series of repeated-measures mixed ANOVAs with planned contrasts (2×2) will be carried out: with intergroup variable (condition - OI × UMC) × intragroup variable (time - pre- and post-) for each dependent variable. More sophisticated multivariate analysis, including multilevel regression, will be used. The effect size of improvement and intention-to-treat (ITT) will be estimated.

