### Sample size

The sample size for this project was based on the effect size found in previous studies [23, 33–35]. In previous RCT online interventions [33] a moderate effect size (g = 0.64) was found [23] when evaluating bodyweight. Taking this into account, a conservative effect size of .64 (Cohen’s d = .64) is expected in primary outcome measures. An estimation of the desired sample size was made based on the expected difference in the primary outcome variables, BP, BMI. Based on a power of 0.80 in a one-tailed test and an alpha of 0.05, 30 participants in each condition would be required. Considering the high levels (around 30 %) of dropout observed in this type of intervention [36], we chose to increase the expected sample to 50 participants in each condition. The hospital where the study took place selected a list of possible patients based on the inclusion and exclusion criteria.

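### The only test specified in detail, a 2×2 pre/post ANOVA, cannot by itself deliver the promised intention-to-treat analysis; the multilevel model already listed should be named for that role

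*Protocol article*

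**What the plan says.** All of this is in the protocol article.

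- **Analysis sets** (Statistical data analysis): "Intention-to-treat and per-protocol analysis will be used". The section ends by saying that an ITT effect will also be estimated. Neither set is ranked above the other.
- **Test given in detail** (same section): "A series of repeated-measures mixed ANOVAs with planned contrasts", with condition as the between-patient factor and two time levels, before and after the intervention, for every dependent variable. The software is SPSS v.20.
- **Further model** (same section): "More sophisticated multivariate analysis, including multilevel regression, will be used". Its outcomes, time points and role are not given, and it is not tied to the ITT analysis.
- **Expected loss** (Sample size): about 30%, described as "dropout observed in this type of intervention". It is not split by arm and not defined as missed outcome visits. The response is a larger sample: "we chose to increase the expected sample to 50 participants in each condition".

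**The concern.** In a two-arm, two-time design the condition × time effect is the difference between arms in mean change. A patient with a baseline value but no 3-month value has no change score, so the repeated-measures ANOVA leaves that patient out unless the value is imputed first. The article therefore promises an analysis of everyone randomised, describes in detail a test that uses only patients measured twice, and expects a substantial share of patients to be lost.

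The sample size reasoning has the same form: recruit more so that enough completers remain. This protects power but not the comparison. If patients leave the web programme for reasons that differ from those in usual care, the remaining patients are no longer balanced by randomisation.

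The two models named could also give different answers, one from about 70 patients and one from 100, and the article does not say which is the trial's result.

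**Working it through.** **1. The plan's own sample size.** Inputs, all from Sample size: d = 0.64, one-tailed alpha 0.05, power 0.80.

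n per arm = 2(1.645 + 0.842)² / 0.64² = 30.2, rounded up to 31. The exact t calculation also gives 31. Power at the stated 30 per arm is 0.798 (normal) or 0.790 (t). The stated 30 is reproduced to within one patient.

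**2. Effect of dropout on numbers.** 30 / (1 − 0.30) = 42.9, so 43 per arm would be enough, and 50 is more than enough. If all dropouts miss the 3-month value, 50 × 0.70 = 35 per arm remain, and 100 × 0.30 = 30 patients leave an unimputed ANOVA.

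**3. Power of the test on those left.** 0.64 × √(35/2) = 2.677, and 2.677 − 1.645 = 1.032, giving power 0.849 (normal) or 0.843 (t). Power is not the issue.

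**4. Size and direction of possible bias.** The article gives no figures for this, so the following is assumed: no true effect; pre/post correlation 0.5; 40% dropout in the intervention arm (SII); 20% at random in usual care (UMC); lower values better. SII dropout rises with either the patient's own poor change or the baseline value, at a log-odds of 0.4, 0.8 or 1.2 per SD. With two time points, a baseline-adjusted comparison (ANCOVA) is the large-sample equivalent of a mixed model with a common baseline mean. Entries are SII minus UMC in outcome SDs; negative values falsely favour the programme.

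| SII dropout driven by | Completer ANOVA contrast | Baseline-adjusted model |
|---|---|---|
| Poor change (partly unobserved) | −0.16, −0.28, −0.38 | −0.12, −0.21, −0.29 |
| High baseline (observed) | +0.08, +0.14, +0.19 | about 0 |

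In the first row, 0.21 / 0.28 = 0.75, so about three quarters of the bias remains under the better model. With SII dropout at 30%, the completer contrast in that row is −0.12 to −0.29. In the second row the completer contrast is wrong in the opposite direction, and the baseline-adjusted model corrects it.

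**5. Check at the trial's own size.** 300 simulated trials of 50 per arm were run with no true effect, correlation 0.7, about 30% dropout overall, SII dropout rising with baseline and UMC dropout random. The completer ANOVA contrast averaged 0.12 SD (Monte Carlo SE 0.01). A mixed model keeping patients with baseline only averaged 0.02 SD (SE 0.01).

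**6. Dilution, as illustration only.** If completers gain 0.64 and SII dropouts gain nothing, the all-randomised effect is 0.64 × 0.80 = 0.51, 0.64 × 0.70 = 0.45 or 0.64 × 0.60 = 0.38 at 20%, 30% or 40% SII dropout.

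**The case against.** The strongest reply is that the text commits to more than the ANOVA. The sentence after it says that multilevel regression will be used, and such a model can keep patients with only a baseline value. Nothing rules out imputing post-tests before the ANOVA. The missing-data method and the definition of the ITT set are commonly left to a full protocol or SAP, neither of which is shown. All of this stands.

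A reader might also infer four stronger things that the article does not support:

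- **That the ANOVA is the primary test.** No analysis is labelled primary. The ANOVA is only the one described in detail.
- **That the ITT analysis is a completer analysis under another name.** This follows only if nothing is imputed and the multilevel model is not the one used for ITT.
- **That 30 of 100 patients will be lost to the test.** The 30% refers to dropout from this kind of intervention. Nothing under Instruments limits the 3-month assessment to programme users, so a patient who stops opening modules can still have blood pressure and weight measured.
- **That the result would be biased in favour of the programme.** The second row of the table shows the opposite direction under an equally simple mechanism.

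Nor does the 0.28 SD figure show what a change of model would gain. Most of that bias comes from the assumed dropout mechanism, and the mixed model shares it.

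What survives is narrower than these readings but is more than missing detail. The article fixes one test in full, and that test alone does not fit the promised analysis under the article's own dropout expectation. A better-suited model is already listed without a role.

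**Conclusion.** The point holds in limited form. Without imputation, the 2×2 ANOVA alone cannot deliver the stated ITT analysis. The number affected is up to about 30 of 100 patients, if expected dropout means missed 3-month assessments. Power is adequate at about 0.84 with 35 per arm, so the exposure is to bias.

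In the assumed scenarios with 40% SII dropout, that bias runs from 0.38 SD in favour of the programme to 0.19 SD against it. A mixed model with a common baseline removes it when dropout depends on observed baseline, and only about a quarter of it when dropout depends on the unobserved outcome. The bias figures and the 0.64-to-0.45 dilution rest on assumed dropout mechanisms. They are not estimates for this trial and do not measure the benefit of the fix.

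**What to change.** In Statistical data analysis:

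1. Name the multilevel model as the primary ITT analysis of blood pressure and BMI: a linear mixed model on all randomised patients, analysed as randomised, with condition × time and a common baseline mean.
2. Label the 2×2 ANOVA and the per-protocol analysis as secondary.
3. Add one sensitivity analysis that imputes missing SII outcomes from UMC. The mixed model relies on dropout depending only on observed data, and this analysis shows how far the conclusion depends on that.

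The cost is a few sentences and some extra programming in SPSS, which is already the chosen software. The effect estimate may be smaller than the completer figure. The article describes the trial as ongoing, so the choice should be recorded before outcome data are analysed.

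### The 2×2 condition × time ANOVA is a valid change-score test, but baseline-adjusted ANCOVA on data already collected would be more precise; the baseline t tests cannot verify randomisation

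*Protocol article*

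**What the plan says.** The section Statistical data analysis takes three steps that bear on this point.

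- It begins with a baseline check whose purpose is to "verify proper randomization (independent samples *t* test for equivalence of groups").
- It then fixes the treatment comparison: "A series of repeated-measures mixed ANOVAs with planned contrasts", in 2×2 form. Condition is crossed with the "intragroup variable (time - pre- and post-) for each dependent variable". No baseline covariate is named.
- It adds that "More sophisticated multivariate analysis, including multilevel regression, will be used", without giving the outcome, the covariates or the role of that model.

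Table 1 in the section Instruments shows that both kinds of primary outcome are measured before and after the intervention: "Blood pressure Omron® Baseline, post-T and follow-ups" and "BMI TANITA Baseline, post-T and follow-ups". The section Sample size uses d = 0.64, a one-tailed alpha of 0.05 and 80% power. It arrives at 30 per condition and raises this to 50 because about 30% are expected to drop out.

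**The concern.** A pre/post ANOVA with two groups looks like a repeated-measures model, but its condition × time term only compares mean change between the arms. It fixes the slope of the final value on the baseline value at 1, whereas ANCOVA estimates that slope from the data. When the true slope is below 1, as regression to the mean implies, the change score subtracts too much of the baseline. Precision is lost, and an arm that happens to start higher appears to improve more. In a trial expecting about 35 completers per arm, both effects can matter for the primary outcomes.

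The baseline t tests do not help. Under random allocation any baseline difference is due to chance, so the tests examine a hypothesis known to be true. A non-significant result does not show equivalence either.

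**Working it through.** **Inputs from the protocol article.** d = 0.64, alpha 0.05 one-tailed, power 0.80, 30 per arm stated, 50 per arm planned, dropout about 30% (all from Sample size). Completers per arm: 50 × 0.70 = 35.

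**Assumptions.** The pre-post correlation ρ is not in the document and is shown as a range. Pre and post SDs are taken as equal, and d is read in SD units of the outcome.

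**The plan's own figure.** n per arm = 2 × [(1.645 + 0.842)/0.64]² = 30.2, which rounds up to 31. The stated 30 is reproduced to within rounding. The calculation is a generic two-group comparison, tied neither to change scores nor to an adjusted analysis.

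**Equivalence of the two tests.** On one simulated data set (35 per arm), the 2×2 condition × time F was 13.4752 and the squared two-sample t on change scores was 13.4752.

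**Variance.** In units of the outcome variance, the effect estimate has variance proportional to
- change score: 2(1−ρ)
- ANCOVA: 1−ρ²

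Ratio = (1−ρ²)/[2(1−ρ)] = (1+ρ)/2, which is below 1 for every ρ below 1. At ρ = 0.5, for example, it is 0.75/1.00 = 0.75.

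**Power** with 35 per arm and d = 0.64, from the noncentral t distribution, change score vs ANCOVA:

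| ρ | Variance ratio | One-sided 0.05 | Two-sided 0.05 |
|---|---|---|---|
| 0.3 | 0.65 | 72% vs 87% | 61% vs 79% |
| 0.5 | 0.75 | 84% vs 92% | 75% vs 86% |
| 0.6 | 0.80 | 91% vs 95% | 84% vs 91% |
| 0.7 | 0.85 | 96% vs 98% | 93% vs 96% |
| 0.9 | 0.95 | about 100% for both | about 100% for both |

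Both columns are needed because the sample size is one-tailed, while an F test on one degree of freedom is non-directional. A simulation of 20,000 trials per ρ agreed with the one-sided column to within about one percentage point.

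**Chance imbalance.** In the same simulation the change-score estimate moved by −0.70, −0.49, −0.30 and −0.10 per unit of baseline difference at ρ = 0.3, 0.5, 0.7 and 0.9, that is, by about −(1−ρ). The ANCOVA estimate moved by about 0. With 35 per arm the chance baseline difference has a standard deviation of √(2/35) = 0.24 SD. At ρ = 0.5 an imbalance of that size shifts the change-score estimate by 0.5 × 0.24 = 0.12 SD, against a planned effect of 0.64 SD.

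**Baseline t tests.** With 50 per arm, a two-sided 5% test detects a 0.3 SD imbalance with probability 32% and a 0.5 SD imbalance with probability 70%. In a correctly randomised trial, three independent tests give at least one p < 0.05 with probability 1 − 0.95³ = 14%, and ten give 1 − 0.95¹⁰ = 40%. The imbalance sizes and numbers of tests are illustrative. Tests on correlated measures such as BMI and body fat are not independent, so the last two figures are only a guide.

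**The case against.** The strongest reply is that the planned test is sound. Allocation is random, so the change-score contrast is unbiased and its type I error is correct. This stands. The sensitivity to imbalance is conditional on the baseline difference actually observed; averaged over randomisation it cancels. A reader might infer that the ANOVA is wrong or biased, and the document does not support that.

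A reader might also infer that the planned analysis falls short of 80% power. That does not follow. The 80% in the article is a one-tailed figure; on that basis the change-score test with 35 completers reaches 84% at ρ = 0.5. Even two-sided it reaches 84% at ρ = 0.6. It falls below 80% only at the lower correlations, and the document does not say which correlation applies. The choice of a one-tailed test is a separate matter and adds no weight here.

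Third, the sentence on multilevel regression might already contain the remedy, since a mixed model with a common baseline mean is such a regression. It could be written that way, and an unseen analysis plan may do so. As printed, it has no outcome, covariates or role, while the ANOVA is specified for every dependent variable. It therefore does not secure the adjustment.

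Last, nothing in the section makes a later analysis depend on the baseline t tests. It would be tempting to say that they will drive the choice of covariates, but the document describes no such step. Their fault is that they cannot do what is asked of them; they alter no treatment estimate.

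**Conclusion.** The point holds as a matter of efficiency. The article fixes a valid analysis where a more precise one is available from the same measurements. The loss depends on ρ: the change-score variance is avoidably large at ρ of 0.3 to 0.7, where ANCOVA cuts it by 35% to 15%, and there is almost nothing to gain at 0.9 or above. If BMI tracks closely over three months and blood pressure less so, both of which are assumptions, the benefit falls mainly on blood pressure. ANCOVA costs one residual degree of freedom. The baseline t tests are a minor accompanying fault. The sample size is not wrong on its own inputs.

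**What to change.** For each continuous outcome, make the primary analysis the adjusted mean difference at 3 months with its 95% CI, from an ANCOVA with condition and that outcome's baseline value as covariate. A mixed model with a common baseline mean would serve equally well, and the multilevel regression sentence could be rewritten to specify it. State that the adjustment is made regardless of how the baseline comparison turns out. Replace the step meant to show that "Relevant statistical analyses will first be performed to verify proper randomization" with a descriptive table of baseline values by arm, without p values.

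No new data or software are needed. Because the article reports the trial as ongoing, this changes a published plan, so it should be dated, justified and documented as an amendment, preferably before outcome data are examined by arm.
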